## Abstract

**Background:**

Patients with type 2 diabetes (T2D) are at increased risk for developing cancer. As approximately 8% of the world’s population is living with T2D, even a slight increase in cancer risk could result in an enormous impact on the number of persons developing cancer. In addition, several glucose lowering drug classes for treating patients with T2D have been associated with a difference in risk of cancer overall, and especially for obesity related cancers. In what way and to what degree cancer risk is modified by the use of different sulfonylureas (SU) is unclear. The primary aim of this study will be to evaluate within-class SU differences in obesity related cancer risk. Secondary aims will be to investigate within-class SU differences in risk for all cancers combined and site-specific cancers separately (i.e. breast, colorectal, prostate, bladder and lung cancer) and to account for duration-response relationships between individual SU use and cancer risk.

**Methods:**

Patients will be selected from a Dutch primary care cohort of patients with T2D linked with the Dutch Cancer Registration (ZODIAC-NCR). Within this cohort study annually collected clinical data (e.g. blood pressure, weight, HbA1c) and nationwide data on cancer incidence are available. Time-dependent cox proportional hazard analyses will be performed to evaluate SU cancer risk, adjusted for potential confounders.

**Discussion:**

This study will be the first prospective cohort study investigating within-class SU differences in cancer risk and could contribute to improved decision making regarding the individual drugs within the class of SUs, and possibly improve quality of life and result in an increased cost-effectiveness of healthcare in patients with T2D.

**Trial registration:**

Nederlands Trialregister (NTR6166), 6 Jan 2017.

## Background

Patients diagnosed with type 2 diabetes (T2D) are at increased risk for developing cancer; especially the risk of obesity-related cancers [1–5]. According to the most recent World Cancer Research Fund (WRCF) definitions obesity related cancers include oesophageal cancer, liver cancer, kidney cancer, stomach cardia cancer, colorectal cancer, advanced prostate cancer, post-menopausal breast cancer, gallbladder cancer, pancreatic cancer, ovarian cancer and endometrial cancer [6].

In addition to T2D and obesity, glucose-lowering agents used in the treatment of T2D have also been associated with cancer risk and some studies have reported that these relations can be drug specific. For example, the use of pioglitazone, not rosiglitazone, has been linked to the development of bladder cancer in some studies [7, 8], although the robustness of the evidence underlying this possible relationship remains unclear and was absent in recent reports [9, 10]. Also, insulin glargine has been linked to higher breast cancer risk in some studies [11], although - again - several studies reported no or even an inverse association [11–13]. Metformin has more consistently been associated with a decreased cancer risk [14], however concerns have been raised that this association might have been influenced by several types of bias [15, 16].

The sulfonylureas (SUs) are one out of six classes of oral glucose-lowering agents advised by the EASD and ADA as a second step when the glycaemic treatment targets are not reached with metformin mono-therapy [17]. Sulfonylureas have been available for many years and are highly efficacious at low costs. In the Dutch primary care treatment guideline for T2D, gliclazide is the preferred SU, as opposed to both the ADA and EASD which do not recommend a specific SU [17]. Previous studies have shown that within the class of SUs differences exist with regard to hypoglycaemia risk [18], for example there have been no reports of severe hypoglycaemia events in gliclazide users [18]. In addition, within-class differences in risk of cardiovascular events and safety when prescribed to patients with renal failure have been reported [19, 20].

An association between the class of SUs and increased overall cancer risk has also been reported [21–24]. Most previous studies are limited by methodological issues, for example many studies reported baseline SU use and did not account for duration of SU use [22–24]. There is also evidence suggesting within-class SU differences in cancer risk, where gliclazide use has been associated with a lower cancer risk [21–24]. There are several potential mechanistic explanations, one of which could be that gliclazide leads to a more selective glucose dependent insulin response and lower insulin levels. In what way and to what degree cancer risk is modified by different SUs in unclear and requires further investigation and confirmation.

Most evidence, however, is derived from small observational cohort studies and substantial knowledge gaps exist. This also holds true for the presumed favourable long-term cancer safety profile of gliclazide in particular. The relations between use of glucose lowering agents and cancer are complex and there is overlap in risk factors; for example, several glucose lowering agents have been associated with weight gain, which in itself has also been related to an increased cancer risk.

The primary aim of this study is to evaluate within-class SU differences in risk for obesity-related cancer (excluding non-melanoma skin cancers) accounting for weight changes during follow-up and drug exposure [6]. Secondary aims are to evaluate within-class SU differences concerning all cancers combined and the cancer risks of the five largest groups of site specific cancers (breast, colorectal, prostate, bladder and lung cancer) accounting for duration of drug use.

## Methods/design

### Data source

This study will be conducted using a combined database of the ZODIAC (Zwolle Outpatient Diabetes project Integrating Available Care) study and NCR (Dutch National Cancer Registration).

#### ZODIAC

The ZODIAC cohort is part of an ongoing primary care prospective study initiated in 1998, in which annually collected data are used for care improvement, benchmarking and research [25]. Patients consented with the anonymous use of their data for study purposes. Patients included are diagnosed with T2D and are exclusively treated in primary care in a shared care setting. Data on age, sex, date of T2D diagnosis, HbA1c, length, weight, estimated GFR, creatinine, albumin-creatinine ratio (ACR), cholesterol/HDL ratio, blood pressure, macrovascular complications (myocardial infarction, TIA, CVA) medication use (both diabetes-specific and other medication), smoking (yes/no) and alcohol use (yes/no) are recorded.

#### NCR

The Netherlands Cancer Registration (NCR) was founded in 1989 and has since recorded almost every cancer event in the Netherlands, and includes incidence date, TNM (tumour, node, metastasis) stage, morphology, location and the therapy received [26]. Basal cell carcinoma of the skin, carcinoma in situ of the cervix, myelodysplastic syndrome and myeloproliferative disorders are all excluded for the NCR database. Benign and borderline tumours are excluded with the following exceptions; benign brain tumours (included from 1999), carcinoids of the appendix (included from 2001), borderline tumours of the ovaries (included from 2001), thymoma (included from 2001), phyllodes tumours (included from 2001) and T-cell leukaemia (included from 2004).

### Study population

#### Combined ZODIAC-NCR cohort

All cancer events that occurred between 1 January 1989 and 2012 were linked to the data of the ZODIAC study via a trusted third party using postal code, full name, date of birth and sex. The medical ethics committee of Isala, Zwolle, the Netherlands approved the linkage of ZODIAC and NCR (METC reference number 13.0765). The NCR expected that the number of false-positive and the number false-negative linkage is both under 1%. By combining the two databases a cohort composed of patients diagnosed with T2D between 1 January 1998 and 31 December 2012 was assembled.

#### Patient selection

The study cohort entry date and baseline date will be the date the patients started participation in the ZODIAC cohort.

#### Inclusion

All patients included will be participating in the ZODIAC-NCR cohort on or after January 1998 and will be users of SUs.

#### Exclusion

Patients treated with long-acting or mixed insulin before oral glucose lowering agents and those receiving insulin on top of SU at study entry will be excluded. Patients who received a cancer diagnosis before receiving a SU will be excluded. For the main analyses patients who switch medication within the class of SUs will be excluded at the time the switch occurs.

#### Follow-up

All patients will be followed from the year of cohort entry until a diagnosis of cancer [3–5]. Patients with no diagnosis of cancer will be censored at the time of death, end of registration within the ZODIAC cohort or end of the study period (31 December 2012), whichever occurred first.

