#### Primary analysis

Descriptive statistics will be used to characterize the patients at cohort entry.

Time dependent cox proportional hazard analyses will be used to estimate the adjusted hazard ratio of developing obesity-related cancer when using gliclazide compared to other SUs (both individual and grouped as non-gliclazide SU). Exposure to SUs will be included as the cumulative number of years exposed to a specific SUs. Exposure status for SU will be updated annually. The primary analyses will be corrected for the previously mentioned confounders measured at baseline.

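### As worded, leaving ZODIAC ends follow-up only for patients without cancer; one end-of-follow-up rule for every patient is needed

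*Protocol article*

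**What the plan says.** The Follow-up section of the protocol article has two sentences. The first covers everyone: "All patients will be followed from the year of cohort entry until a diagnosis of cancer". It does not require that the patient still be registered in ZODIAC. The second gives the censoring times, and its subject is narrower: "Patients with no diagnosis of cancer will be censored at the time of death, end of registration within the ZODIAC cohort or end of the" … The closing words of that second sentence are: "end of the study period (31 December 2012), whichever occurred first". The ordering clause therefore ranks the censoring events of patients without cancer.

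The outcome does not come from ZODIAC. The NCR section says that the registry "has since recorded almost every cancer event in the Netherlands", and the section on the combined cohort says: "All cancer events that occurred between 1 January 1989 and 2012 were linked to the data of the ZODIAC study". Cancers diagnosed after a patient left ZODIAC are therefore in the linked file.

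SU use, by contrast, is known only from ZODIAC records and is updated once a year (Exposure; Primary analysis). Cumulative use is summed up to the time of the event.

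**The concern.** Take two patients who both leave ZODIAC in 2005. One has a registry cancer in 2010, the other stays cancer-free. Under the literal wording the first is an event with follow-up to 2010 and the second is censored in 2005. After exit, the risk set then holds only people who are going to get cancer, so membership of the risk set depends on the future.

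Two things are at stake. Cancer rates are too high in every drug group. And if patients on one SU leave ZODIAC more often than patients on another, that SU gains relatively more such events and looks more harmful when there is no difference. Lower exit on gliclazide would give a spurious protective hazard ratio, which is the direction of the earlier findings cited in the Background. A case after exit also raises an exposure problem: the window for cumulative use runs past the last recorded prescription.

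**Working it through.** **The plan's own figures.** The article states no event count, cancer rate, power or ZODIAC exit rate, so there is nothing to reproduce. All rates below are assumptions. Only the two candidate rules come from the text.

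- Literal rule: a cancer before death and study end always counts; only cancer-free patients are censored at exit.
- Earliest-of rule: everyone's follow-up ends at the first of cancer, death, exit or study end.

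**Step 1: rates.** Let λ be the cancer hazard, μ the death hazard, x the exit hazard (all constant and independent) and τ the maximum follow-up. Write a = λ + μ and b = a + x. Assume λ = 0.015, μ = 0.03, x = 0.05 per year and τ = 10 years, so a = 0.045 and b = 0.095. Per patient:

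- Cancers, literal: (λ/a)(1 − e^(−aτ)) = 0.3333 × 0.3624 = 0.1208
- Cancers before exit: (λ/b)(1 − e^(−bτ)) = 0.1579 × 0.6133 = 0.0968
- Years registered: (1 − e^(−bτ))/b = 0.6133/0.095 = 6.455
- Extra years after exit, future cases only: λ[A − (B − C)/x], where A, B and C are the integrals from 0 to τ of t·e^(−at), e^(−at) and e^(−bt). This is 0.015 × [37.25 − (8.053 − 6.455)/0.05] = 0.080

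The earliest-of rate is 0.0968/6.455 = 15.0 per 1000 person-years, the true value. The literal rate is 0.1208/(6.455 + 0.080) = 18.5 per 1000. The literal rule adds 0.0240 cancers per patient but only 0.080 person-years. The same formula gives 17.0 at 3% exit and 22.3 at 10% exit, so the excess is +14% to +49% over 10 years. A simulation with 1,000,000 patients per group agrees.

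With a second set of assumptions (cancer 1.2% and death 2.5% per year, entry uniform over 1998–2011, hence 1 to 15 years of follow-up), 5% exit raises the rate from 12.0 to 14.7 per 1000.

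**Step 2: hazard ratio.** At time s a group's literal risk set is the registered fraction, e^(−(a+x)s), plus (1 − e^(−xs)) times the probability of a cancer after s that precedes death and study end. The number of cancers at s does not depend on x, but the risk set shrinks as x grows. Two groups with the same λ and different x therefore get a hazard ratio away from 1. Results with a true hazard ratio of 1.00:

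| Exit per year, gliclazide vs other | 1–15 years, cancer 1.2%, death 2.5% (large-sample limit) | 10 years, cancer 0.8% or 1.5%, death 3% (simulated) | 14 years, same rates (simulated) |
|---|---|---|---|
| 5% vs 5% | 1.00 | 1.00–1.01 | 1.01 |
| 3% vs 5% | – | 0.92 | 0.89–0.90 |
| 4% vs 6% | 0.92 | – | – |
| 3% vs 6% | 0.88 | 0.88 | 0.84–0.85 |
| 5% vs 8% | 0.88 | – | – |
| 5% vs 10% | – | 0.80–0.81 | 0.75–0.76 |
| 6% vs 3% | 1.14 | – | – |
| 8% vs 4% | – | 1.19–1.21 | 1.26–1.28 |

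The first results column solves the Cox score equation with the risk sets above, averaged over follow-up, and has no simulation noise. Simulations of the 3% versus 6% case under the same assumptions gave 0.86 to 0.87. In the run that gave 0.860, complete follow-up of the same cohorts gave 0.977, so part of the gap from 1 is noise (0.860/0.977 = 0.88). Over only 5 years the 3% versus 6% case gives 0.93 to 0.94.

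With equal exit, real effects are also preserved under the literal rule: a true 0.70 gives 0.70–0.71 and a true 0.80 gives 0.80–0.81. The earliest-of rule recovers the true hazard ratio in every independent-exit scenario, to within simulation error.

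**Step 3: events lost by the earliest-of rule.** The share is 1 − (cancers before exit)/(cancers, literal), pooled over both groups and averaged over 1 to 15 years of follow-up. It is 17% at 3% vs 6%, 19% at 5% vs 5% and 24% at 5% vs 8%.

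**The case against.** The strongest reply is that this is ordinary shorthand. In a condensed article, patients with no cancer usually means those with none by the time they leave. One clause covers death, exit and study end together, and the linkage sentence describes how the database was built, not which cancers are endpoints. The design also points this way: SU exposure is defined within ZODIAC, and the secondary analyses use time-varying confounders only while follow-up exists. Modelling the years after exit would need a carry-forward rule that the article does not give. All of this stands, and on that reading the rule has no fault. But no sentence says that cancers after exit are ignored, and the two readings give different estimates.

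It also stands that the planned effect measure is a hazard ratio, so inflated rates alone would not distort the main result. The calculations compare two fixed drug groups, without the time-updated cumulative exposure, the one-year lag or the removal of patients who switch SU. Their sizes illustrate the mechanism and do not predict the study's bias.

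A reader might go further and infer that exit is health-related, so that even the earliest-of rule needs censoring weights. ZODIAC is described thus: "Patients included are diagnosed with T2D and are exclusively treated in primary care in a shared care setting". Referral out might therefore end registration, and for the main model the article says: "The primary analyses will be corrected for the previously mentioned confounders measured at baseline". The documents do not carry this. That referral ends registration is an inference. Simulated hazard ratios under SU-dependent, health-related exit were only 1.03 to 1.06, with simulation error of 0.02 to 0.03. A weighted sensitivity analysis is something that an article may leave to the full plan.

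**Conclusion.** The point holds as a defect of wording with a possible consequence. The literal Follow-up rule makes censoring depend on the future outcome, and nothing else in the article rules that reading out. If it were applied, rates would be too high in every group (about +14% to +49% over 10 years at 3% to 10% annual exit). The hazard ratio could be biased in either direction if exit differs by SU: about 0.87 to 0.88 instead of 1.0 at 3% versus 6%, and about 1.14 at 6% versus 3%.

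A reader might infer that the gliclazide hazard ratio will be biased, or that the investigators chose a biased rule. The article supports neither. With equal exit the hazard ratio is essentially unbiased, no exit rates by SU are given, and the usual rule may be what was meant. Every size here rests on assumed, constant and independent cancer, death and exit rates.

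**What to change.** Replace the two Follow-up sentences with one rule for every patient: follow-up ends at the earliest of endpoint cancer, death, end of ZODIAC registration or 31 December 2012. Add that registry cancers dated after a patient's end of registration are not events in the main analysis. Report the rate of ZODIAC exit by SU, so that readers can see whether the hazard ratio was at risk.

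The cost is a change of wording and one descriptive table from data already held. If the usual rule was always intended, no events are lost. If the literal rule was intended, about 17% to 24% of counted events drop out under the assumed exit rates and confidence intervals widen somewhat.

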#### Study endpoints

The primary outcome will be within-class SU difference in obesity-related cancer risk (see Table 1 for included cancers). The secondary outcomes will be all cancer risk (Table 2), site-specific cancer risk and the presence of a duration response relationship between SU use and cancer. Cancer sites of special interest will be specific cancers of the breast, colorectal, bladder, advanced prostate and lung cancer. Study endpoints will be evaluated for men and women separately.

**Table 1 Tab1:** Cancers included in primary endpoint obesity related cancer

Men	Women
Oesophageal (adenocarcinoma)	Oesophageal (adenocarcinoma)
Stomach cardia	Stomach cardia
Kidney	Kidney
Gallbladder	Gallbladder
Liver	Liver
Pancreatic	Pancreatic
Colorectal	Colorectal
Prostate cancer	Ovarian
	Breast
	Endometrial

**Table 2 Tab2:** Cancer excluded from secondary endpoint all cancer risk

Men (cancers excluded)	Women (cancers excluded)
Non-melanoma skin cancer	Non-melanoma skin cancer
Breast	Prostate
Ovarian	Male genital organs
Endometrial	
Female genital organs	

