#### Secondary analyses

In a secondary analyses changes diabetes medication during follow-up will be accounted for. Time dependent cox proportional hazard analyses will be used to estimate the adjusted hazard ratio of developing all cancer when using gliclazide compared to other SUs (both individual and grouped as non-gliclazide SU). Exposure to confounders (including concurrent metformin and insulin use) will be handled as time varying variables where follow-up is available. The updated mean method will be used for HbA1c, BMI and serum creatinine. These analyses will be repeated to investigate the adjusted hazard ratio of breast, colorectal, prostate, bladder and lung cancer.

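### Table 1 counts all prostate and all breast cancers in the primary endpoint, whereas the definition cited for the primary aim covers only advanced prostate and post-menopausal breast cancer

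*Protocol article*

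**What the plan says.** The Background takes its list of obesity-related cancers from one cited source (reference 6). In that list two sites are qualified by stage or menopausal status: "advanced prostate cancer, post-menopausal breast cancer, gallbladder cancer". The primary aim, at the end of the Background, cites the same reference.

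Study endpoints makes Table 1 the operative list: "The primary outcome will be within-class SU difference in obesity-related cancer risk (see Table 1 for included cancers". The table's title is "Cancers included in primary endpoint obesity related cancer". For men it has prostate cancer with no stage limit. For women it has breast with no menopausal or age limit. It does limit oesophageal cancer to adenocarcinoma and stomach cancer to the cardia.

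For the site-specific secondary endpoints, Study endpoints says: "Cancer sites of special interest will be specific cancers of the breast, colorectal, bladder, advanced prostate and lung cancer". The Abstract and the secondary aims name prostate cancer without the word advanced, and so does the analysis section: "These analyses will be repeated to investigate the adjusted hazard ratio of breast, colorectal, prostate, bladder and lung cancer".

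The section on the cancer registry (NCR) says that its record "includes incidence date, TNM (tumour, node, metastasis) stage, morphology, location and the therapy received".

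**The concern.** The study's main claim will be about obesity-related cancer. Table 1 as it stands counts cancers that the cited definition leaves out, and the article does not explain the wider list. Endpoints are evaluated for men and women separately, so the prostate entry bears wholly on the men's analysis and the breast entry wholly on the women's.

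Two things are at stake. First, the reported primary result would not describe the outcome that the aim names. Second, with two definitions in one document, a choice between them after the data are seen would leave room for selective reporting. None of the six sensitivity analyses varies the endpoint definition, so the plan as written would not show how much the choice matters.

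For the site-specific prostate endpoint the text is ambiguous: an analyst following Study endpoints and one following Secondary analyses would count different events.

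**Working it through.** **1. The texts side by side**

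| Place in the protocol article | Prostate | Breast |
|---|---|---|
| Background, cited definition | advanced only | post-menopausal only |
| Table 1, primary endpoint | no restriction | no restriction |
| Study endpoints, site-specific text | advanced | no restriction |
| Abstract, secondary aims, Secondary analyses | no restriction | no restriction |

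Table 1 is unlikely to be mere shorthand. The Background names oesophageal cancer without histology and Table 1 adds the adenocarcinoma limit, so the table does carry qualifiers where its authors wanted them.

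**2. Can the restriction be applied?**

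- Prostate: the registry records TNM stage, so advanced disease can be identified. The article does not say how complete the stage data are.
- Breast: age and incidence date are available, but menopausal status is not among the variables listed for the cohort. An age-at-diagnosis proxy would be needed.
- Follow-up: the Follow-up section ends observation at a diagnosis of cancer. It does not say what happens at a cancer that lies outside the endpoint, so narrowing Table 1 calls for a rule.

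**3. What the wider list could do to the hazard ratio**

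The article states no sample size, event count, target hazard ratio or power, so there is no figure to reproduce. The following is an illustration, and every input is an assumption:

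- true HR on qualifying cancers h = 0.75, gliclazide against other sulfonylureas;
- HR of 1 on non-qualifying cancers;
- two groups of equal size;
- p = non-qualifying cancers as a share of all counted events, from 5% to 40%.

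Set the qualifying rate to 1 in the comparison group and h in the gliclazide group, and let n be the non-qualifying rate in each group. Then:

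- p = 2n / (1 + h + 2n), so n = [(1 + h)/2] × p/(1 − p) = 0.875 × p/(1 − p)
- HR of the mixed endpoint = (h + n)/(1 + n)
- total events needed for equal power, relative to the restricted endpoint: R = (ln h / ln HR_mixed)²
- net of the extra events that the wider list supplies: R × (1 − p)
- information loss = 1 − 1/[R × (1 − p)]

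Example at p = 20%: n = 0.875 × 0.25 = 0.219; HR = 0.969/1.219 = 0.795; R = (0.2877/0.2296)² = 1.57; net = 1.57 × 0.8 = 1.26; loss = 1 − 1/1.256 = 20%.

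| p | n | mixed HR | R | net ratio | information loss |
|---|---|---|---|---|---|
| 5% | 0.046 | 0.761 | 1.11 | 1.05 | 5% |
| 10% | 0.097 | 0.772 | 1.24 | 1.11 | 10% |
| 20% | 0.219 | 0.795 | 1.57 | 1.26 | 20% |
| 30% | 0.375 | 0.818 | 2.06 | 1.44 | 30% |
| 40% | 0.583 | 0.842 | 2.80 | 1.68 | 41% |

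**4. The opposite assumption**

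If the sulfonylurea effect is the same on the extra cancers, the HR stays at 0.75 and the events rise by a factor 1/(1 − p). Starting from 80% power (two-sided 5% level), power is Φ(2.802/√(1 − p) − 1.960). At p = 10% this is 84%, and at p = 40% it is 95%.

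**The case against.** A reader might infer that Table 1 as written does dilute the primary contrast. The document does not support that as a fact. Dilution requires a null or weaker sulfonylurea effect on non-advanced prostate and pre-menopausal breast cancer, and nothing in the article says so. The comparison is drug against drug, and the mechanism offered in the Background is insulin response and insulin levels, with no distinction by stage or menopausal status. Under an equal effect the wider list gains power. This objection stands, and it makes the consequence conditional.

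A reader might also infer that localised prostate cancers bring in detection bias. The article shows a general concern about detection around the start of treatment, which it addresses with the one-year lag, the alternative lags and the exclusion of first-year events. It gives no reason why screening should differ between sulfonylureas, and such bias has no fixed direction. That reading is not supported.

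Three further points stand in part. Pre-menopausal breast cancers are probably few in type 2 diabetes (an assumption, since no age distribution is given), so the upper values of p have little support for women. The primary endpoint can be executed as written, because the text points expressly to Table 1; the ambiguity between analysts concerns the site-specific prostate endpoint. Detailed stage coding may properly sit in an analysis plan that is not shown. None of these removes the mismatch: Table 1 states a different endpoint from the cited definition, and this is not a detail left for later.

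**Conclusion.** The contradiction holds for both sites and touches the primary endpoint. Table 1 counts cancers that the definition cited for the primary aim excludes, and the site-specific prostate endpoint has two versions. The case for correction rests on this mismatch and on the lack of any sensitivity analysis that varies the endpoint. It does not rest on a proven loss of power.

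The size is unknown, because the article gives neither event counts nor a sulfonylurea effect by stage or menopausal status. With a true HR of 0.75, no effect on the extra cancers, equal groups and a share of 5% to 40% of all counted events, the HR would be about 0.76 to 0.84 and the information loss about 5% to 41%. With an equal effect there is no dilution and power rises. Non-advanced prostate cancer, in the men's analysis, is probably the larger part of the problem.

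**What to change.** 1. In Table 1, enter prostate cancer as advanced, with an explicit rule based on the registry's TNM stage and a rule for missing stage. Enter breast cancer as post-menopausal, with a fixed age-at-diagnosis proxy, because menopausal status is not a listed variable.
2. State how follow-up is handled when a patient has a cancer outside the endpoint, since Follow-up now ends at a cancer diagnosis.
3. Use one prostate definition in the Abstract, the aims, Study endpoints and Secondary analyses.
4. Report the unrestricted prostate and breast endpoint as a prespecified sensitivity analysis.

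A sound alternative is to keep the broad list, say why it departs from the cited definition, and prespecify the restricted definition as the sensitivity analysis. Points 2 and 3 still apply, point 2 then to that sensitivity analysis.

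The cost is protocol wording and a registry filter. The restricted endpoint will have fewer events, and the age proxy and missing stage will cause some misclassification.
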